#### **8.1.4. Pharmacokinetic Statistical Analyses**

##### **8.1.4.1. Dose Proportionality**

Dose-proportionality of plasma TLC-2716 and its metabolites, PK parameters,  $C_{\max}$ ,  $AUC_t$ ,  $AUC_{\text{tau}}$ , and  $AUC_{\text{inf}}$ , as applicable for Part A, Part B, and Part C (as applicable) over the dose range tested will be investigated. A power regression model will be fitted to describe the relationship between Y ( $C_{\max}$ ,  $AUC_{\text{tau}}$ ,  $AUC_{\text{last}}$ , and  $AUC_{\text{inf}}$ ) and X (dose) under fasting conditions. The model is defined as:

$$\ln(Y) = \beta_0 + \beta_1 \ln(X), \text{ where Y is PK parameter and X is dose}$$

The null hypothesis that will be tested is that the AUCs and  $C_{\max}$  values are dose-proportional, or slope  $\beta_1=1$  is within 90% CI of the slope.

An alternative evaluation of dose proportionality may be conducted using analysis of variance (ANOVA) on dose normalized, natural log-transformed AUC and  $C_{\max}$  of TLC-2716 and its metabolites. The model will include dose as a fixed effect. The two-sided 90% CI for the ratio of dose comparisons will be constructed.

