### 1.2.3. Nonclinical Pharmacokinetics (PK)

Absorption, distribution, metabolism, and elimination of TLC-2716, as well as the potential for drug-drug interactions, were assessed *in vitro* and *in vivo* in preclinical models. The pharmacokinetic (PK) profile indicates limited systemic exposure, with undetectable plasma levels 2-4 hours after dosing, and high levels in the liver consistent with rapid transporter-mediated uptake into hepatocytes.

TLC-2716 is a lipophilic, small molecule, LXR inverse agonist with a high binding affinity to plasma proteins (> 99%) in humans, mice, rats, dogs, and monkeys. Following intestinal absorption into the portal vein, TLC-2716 is highly extracted by the liver (92% hepatic extraction ratio in rats). Consistent with high liver loading, systemic exposure of TLC-2716 was generally low following oral administration in multiple species. In rodents, TLC-2716 was predominantly distributed to the liver and intestine; brain distribution data suggest that little or no TLC-2716-derived compounds cross the blood-brain barrier. *In vitro*, TLC-2716 was stable in primary hepatocytes from human, mouse, and dog. Together with the metabolites observed in

livers from preclinical species *in vivo*, the biotransformation pathway of TLC-2716 appears to involve oxidation, deamination, desulfation, glucuronidation, and taurine conjugation.

In *in vitro* studies, TLC-2716 was not a substrate of CYP1A2, CYP2B6, CYP2C8, CYP2C9, CYP2C19, CYP2D6, or CYP3A5, however, it was a modest substrate of CYP3A4 suggesting that co-administration of CYP3A4 inhibitors or inducers may affect the exposure of TLC-2716. TLC-2716 did not inhibit CYP1A2, CYP2C19, or CYP2D6, but demonstrated weak to modest inhibition of CYP2B6, CYP2C8, CYP2C9, and CYP3A4. In primary human hepatocytes, TLC-2716 induced CYP2B6 and CYP3A4 (> 2-fold relative to control), and therefore, may alter the exposures of co-administered substrates of these CYP enzymes *in vivo*. Finally, inhibition of P-gp, BCRP, OATP1B1, and OATP1B3 by TLC-2716 was observed *in vitro* at 10  $\mu$ M. While these findings suggest that TLC-2716 may alter the exposure of concomitant medications (and vice versa), the unique PK profile of TLC-2716, characterized by minimal systemic exposure and high protein binding, may reduce the potential for clinically relevant drug-drug interactions. Additional studies will be conducted to evaluate the clinical relevance of these findings.

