### 1.3.2. Rationale for Dose Selection

In this FIH study, oral doses of TLC-2716 ranging from 0.5 mg to a maximum of 50 mg per day (a 100-fold dose range) will be evaluated in healthy subjects. These doses were selected to provide predominantly liver exposure and minimize the potential for adverse effects mediated by systemic exposure (e.g., impact on reverse cholesterol transport). A starting dose of 0.5 mg and a maximum dose of 50 mg provide 672- and 6.7-fold safety margins based on the NOAEL observed in the 4-week GLP toxicity study in monkeys, the most sensitive preclinical species evaluated (Table 1). Based on pre-clinical pharmacology data, it is expected that doses at the lower end of this range will demonstrate efficacy for relevant clinical parameters based on the preferential liver distribution of TLC-2716. For example, in the DIO mouse and HFD-fed ZDF rat models, a daily TLC-2716 dose of 1 mg/kg administered for 2-3 weeks led to significant reductions in liver TG, plasma TG, and cholesterol concentrations. Based on allometric scaling for mice and rats, this dose is equivalent to a human equivalent dose (HED) of approximately 6 to 11 mg per day in a 70-kg human.

**Table 1. Estimated Dose Margins Following Oral Administration of TLC-2716 Based on 4-week, GLP Chronic Toxicology Studies**

| Species | Duration of Dosing (Days) | NOAEL (mg/kg/day) | AUC 0-24 (ng.h/mL)    | Human Equivalent NOAEL (mg) a | Dose Margins b |       |       |
|---------|---------------------------|-------------------|----------------------------------|------------------------------------------|---------------------------|-------|-------|
|         |                           |                   |                                  |                                          | 0.5 mg                    | 20 mg | 50 mg |
| Mouse   | 28                        | 80                | 149.13 (male)
162.11 (female) | 455                                      | 910                       | 22.8  | 9.1   |
| Monkey  | 28                        | 15                | 51.08 (male)
74.09 (female)   | 336                                      | 672                       | 16.8  | 6.7   |

AUC0-24 = area under the plasma concentration-time curve from time 0 to 24 hours concentration; FIH = first-in-human; HED = human equivalent dose; NOAEL = no-observed-adverse-effect-level

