### **8.7. Pharmacokinetic Analysis**

Plasma concentrations and PK parameters (e.g.,  $AUC_{last}$ ,  $AUC_{inf}$  [single-dose],  $\%AUC_{exp}$  [single dose],  $CL/F$  [single dose],  $AUC_{tau}$  [multiple-dose],  $C_{tau}$  [multiple-dose],  $CL_{ss}/F$  [multiple dose], and  $V_z/F$ ,  $C_{max}$ ,  $T_{max}$ ,  $C_{last}$ ,  $T_{last}$ ,  $\lambda_z$ ,  $CL/F$ , and  $t_{1/2}$ , if applicable) will be listed and summarized for TLC-2716 (and its metabolites, as applicable) using descriptive statistics by treatment for each cohort.

Dose proportionality will be assessed by comparing PK parameters of TLC-2716 across evaluated dose levels. A power model will be fitted using all doses across cohorts to evaluate the dose proportionality based on  $AUC_{last}$ ,  $AUC_{inf}$  (single-dose),  $AUC_{tau}$  (multiple-dose),  $C_{tau}$  (multiple-dose), and  $C_{max}$ . The population mean slope will be estimated with a 90% confidence interval. An alternate evaluation of dose proportionality may be conducted using analysis of variance (ANOVA) on dose normalized, natural log-transformed AUC,  $C_{tau}$  (multiple-dose), and  $C_{max}$ . Dose proportionality analyses will be conducted separately for the single- and multiple-dose cohorts.

Additional analyses such as accumulation ratio and time to steady state may be conducted as appropriate. If fasted cohorts are conducted in Part C, an evaluation of the effect of fasting status on TLC-2716 PK may be conducted.

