#### 1.2.1. Part A: Single-Ascending Dose [SAD] (Cohorts 1-5)

Part A will evaluate the safety, tolerability, PK, and PD of single-ascending doses of oral TLC-2716 or placebo-to-match (PTM) under fed conditions. Part A will proceed in up to 5 dose-escalation cohorts and will be governed by a review of safety and tolerability, any relevant and available PK and/or PD data, and study-specific stopping criteria.

Within each cohort, 10 unique subjects will be randomized 4:1 to receive either blinded TLC-2716 (N = 8) or PTM (N = 2). All study drugs in Part A will be administered in the morning following a standard meal.

At the initiation of each cohort in Part A, prior to randomization of the entire cohort, two sentinel subjects will be randomized, one to TLC-2716 at the dose to be evaluated in the planned cohort, and one to corresponding PTM. Enrollment and randomization of the remaining eight subjects in each cohort will be determined upon evaluation of all safety and tolerability data through Day 2 for these two sentinel subjects.

For Cohorts 2-5, initiation of single-dose administration will be permitted after evaluation of cumulative blinded safety data, and any relevant and available PK and/or PD data up to and including Day 4, following single-dose administration of the previous cohort.

The cohorts and study treatments for Part A are as follows:

| Cohort | Day 1                                                                    |
|--------|--------------------------------------------------------------------------|
| 1      | 0.5 mg TLC-2716 (1 x 0.5 mg) or PTM capsule SD, fed                      |
| 2      | 2 mg TLC-2716 a (1 x 2 mg) or PTM capsule SD, fed             |
| 3      | 6 mg TLC-2716 a (3 x 2 mg) or PTM capsules SD, fed            |
| 4      | 12 mg TLC-2716 a (2 x 5 mg; 1 x 2 mg) or PTM capsules SD, fed |
| 5      | 20 mg TLC-2716 a (4 x 5 mg) or PTM capsules SD, fed           |

PTM = placebo-to-match; SD = single dose.

a The planned doses may be modified based on the observed safety, tolerability, and any relevant and available PK and/or PD data. Any modified dose will be within 3-fold of a dose previously tested.

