## **8. PHARMACOKINETIC ANALYSIS**

### **8.1.1. Data Handling**

All PK analyses will use the PK Analysis Set. Plasma concentrations and plasma PK parameters will be listed and summarized for TLC-2716 and its metabolites (TLC-6665, TLC-7255), as applicable using descriptive statistics by treatment and PK Day (as applicable) for each cohort. Plasma concentration versus time curves will also be presented.

Plasma concentrations that are below the limit of quantification (BLQ) will be treated as zero for calculation of descriptive statistics. When all concentrations are BLQ for a timepoint, the mean BLQ concentrations will be presented as BLQ, and the SD and CV will be reported as not applicable.

For PK parameter calculation, BLQ values prior to a quantifiable concentration will be treated as zero. BLQ values between 2 quantifiable concentrations, or in the terminal phase will be set as missing. If consecutive BLQ concentrations in the terminal phase are followed by quantifiable concentrations, those concentrations after consecutive BLQ concentrations will be treated as missing.

No missing data imputation will be performed.

Missing concentrations will be treated as missing from the descriptive statistics and PK parameter calculations.

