### 8.1.3. Plasma Pharmacokinetic Parameters

The plasma concentration-time data for TLC-2716 and its metabolites will be analyzed by noncompartmental analysis using Phoenix® WinNonLin® Version 8.3.4 or higher (Certara USA, Inc., Princeton, NJ). The following single- and multiple-dose PK parameters will be calculated for TLC-2716 and its metabolites as applicable based on actual times, where data permit:

| PK Parameter   | Definition                                                                                                |
|----------------|-----------------------------------------------------------------------------------------------------------|
| $C_{max}$      | Maximum observed plasma concentration                                                                     |
| $t_{max}$      | Time of maximum observed concentration                                                                    |
| $t_{last}$     | Time of last measurable concentration                                                                     |
| $AUC_{last}$   | AUC from time 0 to the last quantifiable concentration, calculated using the linear trapezoidal rule      |
| $AUC_{inf}$    | AUC from time 0 extrapolated to infinity, calculated using the linear trapezoidal method                  |
| $AUC_{tau}$    | Area under the concentration-time curve for one dosing interval (tau). (Day 1 and Day 14 for MAD cohorts) |
| $t_{1/2}$      | Apparent terminal elimination half-life, calculated as: $\ln(2) / K_{el}$                                 |
| CL/F           | Apparent total body clearance, calculated as: $Dose / AUC_{inf}$                                          |
| $V_z/F$        | Volume of distribution during the terminal phase, calculated as: $Dose / [K_{el} * AUC_{inf}]$            |
| $AR_{C_{max}}$ | Accumulation ratio based on $C_{max}$ , calculated as: $C_{max} (Day 14) / C_{max} (Day 1)$               |
| $AR_{AUC}$     | Accumulation ratio based on $AUC_{tau}$ , calculated as: $AUC_{tau} (Day 14) / AUC_{tau} (Day 1)$         |

In addition to the above PK parameters, which will be listed and summarized, the following parameters will also be listed to document the selection of data points used to estimate  $t_{1/2}$  using non-compartmental procedures:

| PK Parameter     | Definition                                                                                                                             |

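### If the lowest doses lie near the assay limit, the slope-1 test on AUClast can read dose-proportional PK as supra-proportional

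*Combined protocol and SAP*

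**What the plan says.** SAP 8.1.4.1: "A power regression model will be fitted to describe the relationship between Y" (Cmax, AUCtau, AUClast and AUCinf) and dose, as ln(Y) = β0 + β1 ln(X). The null is dose proportionality, judged by whether slope 1 "is within 90% CI of the slope". A dose-normalised ANOVA is the optional alternative.

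SAP 8.1.3 defines AUClast as "AUC from time 0 to the last quantifiable concentration, calculated using the linear trapezoidal rule". SAP 8.1.1 adds that "BLQ values between 2 quantifiable concentrations, or in the terminal phase will be set as missing", so nothing is accrued after the last quantifiable sample.

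Protocol 8.7: "A power model will be fitted using all doses across cohorts to evaluate the dose proportionality based on" a list that includes AUClast, with single- and multiple-dose cohorts analysed separately. Doses start at 0.5 mg and reach 20 mg in Parts A and B, and up to 50 mg in Part C.

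The SAP lists the extrapolated share of AUCinf and the points used for Kel, and summarises tlast. It sets no limit on extrapolation, defines no common-interval AUC, and does not say which slope governs when they disagree.

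**The concern.** The stated null is proportional exposure. What the AUClast slope actually tests is proportional exposure together with an equal quantified fraction at every dose. The second condition fails when a fixed LLOQ cuts low-dose profiles short. Under first-order decline and exact proportionality, a 0.5 mg profile reaches any given concentration log2(20/0.5) = 5.3 half-lives before a 20 mg profile. The quantified fraction then rises with dose and pushes the slope above 1. The BLQ rule used for the summary tables does not alter this.

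This compound makes the question a fair one. Protocol 1.2.3 describes limited systemic exposure, "with undetectable plasma levels 2-4 hours after dosing", in preclinical work. PK is a primary objective, AUClast is among the primary endpoints in protocol 8.1.2, and protocol 1.3 says the results will support Phase 2 dose selection. An assay artefact could be reported as greater-than-proportional systemic exposure for a drug intended to have little of it.

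**Working it through.** The plan states no slope, power or error figure, so there is none to reproduce.

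**Inputs from the documents.** Doses 0.5, 2, 6, 12 and 20 mg; 8 active subjects per dose; the SAP 8.1.2 single-dose sampling times to 72 h; linear trapezoid to the last quantifiable sample; terminal BLQ missing; 90% CI rule (5% in each direction).

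**Assumed, because the documents do not give them.** LLOQ, expressed as a fraction q of the typical 0.5 mg Cmax; half-life 1, 4 or 12 h; between-subject exposure CV 40% (range 20-80%); absorption rate 2/h; 20% variability on elimination rate; 10% residual error.

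**Hand check.** Take a mono-exponential decline with continuous sampling. The area lost after the LLOQ is LLOQ/ke, which as a fraction of AUC at dose D is q × 0.5/D. With q = 20%:

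| Dose (mg) | Captured fraction | ln(captured) | ln(dose) minus mean |
|---|---|---|---|
| 0.5 | 0.800 | −0.2231 | −2.148 |
| 2 | 0.950 | −0.0513 | −0.761 |
| 6 | 0.983 | −0.0168 | 0.337 |
| 12 | 0.992 | −0.0084 | 1.030 |
| 20 | 0.995 | −0.0050 | 1.541 |

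- Slope bias = sum of cross-products / sum of squares = 0.496/8.743 = 0.057.
- SD of log AUC = √(ln(1 + 0.4²) + 0.2²) = 0.434.
- Slope SE = 0.434/√(8 × 8.743) = 0.052.
- The shift is 0.057/0.052 = 1.1 SE. Upward rejection is about 1 − Φ(1.686 − 1.09) = 28%, against a nominal 5%.

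**Simulation under exact proportionality** (one-compartment oral model, CV 40%, 200-1000 trials per setting). AUClast mean slope and upward rejection:

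| LLOQ / Cmax at 0.5 mg | Half-life 1 h | Half-life 4 h |
|---|---|---|
| 1% | 1.014, 10% | 1.013, 8% |
| 5% | not tabulated | 1.041, 18% |
| 10% | 1.028, 13% | 1.062, 28% |
| 20% | 1.041, 18% | 1.103, 55% |
| 50% | 1.137, 64% | 1.197, 89% |

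- With no LLOQ (half-life 4 h) the slope was 1.001, with 6.2% rejected upward and 5.0% downward. The excess therefore comes from truncation.
- A separate set of runs gave 8-17% at LLOQ 1-5% of Cmax, 14-28% at 10%, 21-50% at 20% and 60-86% at 50%. The ranges quoted in the conclusion combine the two sets.
- Half-life 12 h: 6% at 1%, 32% at 10%, 53% at 20%, 96% at 50%.
- CV sensitivity (half-life 4 h, LLOQ 20% of Cmax): 83% at CV 20%, 41% at 60%, 26% at 80%.
- Adding a 50 mg level (half-life 4 h): 8% at 1%, 27% at 10%, 91% at 50%.
- At half-life 4 h and LLOQ 50% of Cmax, AUClast captured about 49% of true AUC at 0.5 mg and about 100% at 20 mg.

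**Other endpoints.** The Cmax slope stayed at about 0.99-1.00 with near-nominal error. AUCinf was near nominal with LLOQ up to 20% of Cmax. At 50% it was rejected downward in 19-41% of trials, because low-dose subjects with too few terminal points dropped out.

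**Is a low margin plausible?** As an illustration only, scale protocol Table 1 linearly:

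- AUC at 0.5 mg is 51.08 × 0.5/336 = 0.076 to 74.09 × 0.5/336 = 0.110 ng·h/mL.
- With half-life 1 h and absorption 2/h, tmax = ln(2/0.693)/(2 − 0.693) = 0.81 h.
- Cmax = 0.693 × e^(−0.693 × 0.81) × AUC ≈ 0.395 × AUC, or about 0.03-0.04 ng/mL.
- An LLOQ at 10% of Cmax would then have to be about 0.003-0.004 ng/mL.

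This assumes equal exposure at equivalent dose and linearity over a 672-fold range.

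**Does the remedy work?** A common-interval AUC returned upward rejection to about 5-8% with LLOQ 5-30% of Cmax, and to about 15% at 50%. The treatment of subjects whose tlast falls before the end of the interval matters. Setting them missing gave 8-20% downward rejection at LLOQ 10-50% of Cmax; integrating them to their own tlast gave 4-14% upward.

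**The case against.** The best defence is that nothing shows the 0.5 mg cohort will lie near the LLOQ. The preclinical remark on undetectable levels gives no dose or assay limit, and the Table 1 scaling is a long extrapolation. With an LLOQ at 1% of Cmax the excess is small. This stands: a reader might infer that proportional PK will be rejected, and the documents do not support that.

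The plan also supplies material for spotting the artefact. Cmax and AUCinf are modelled beside AUClast, tlast is summarised, %AUCextrap and the Kel points are listed, and the SAP's PK Analysis Set requires enough data for reliable parameters. A slope above 1 on AUClast alone, with tlast rising by dose, would be visible. That also stands, but these are informal diagnostics and no rule says how discordant slopes are read.

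Three further readings are tempting and should be resisted.

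- **That the artefact would mislead Part C dosing.** No section ties the power model to Part C. Protocol 8.2.1 rests those decisions on review of available safety, PK and PD data, the final analysis follows completion of all subjects, and SAP 10 plans no interim analysis.
- **That protocol 8.7 gives AUClast priority by naming it first.** Order of listing is not a hierarchy, and SAP 8.1.4.1 names Cmax first.
- **That AUCinf can simply replace AUClast.** It fails in the opposite direction when the lowest dose is barely quantifiable.

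**Conclusion.** The concern holds as a conditional statement about one of four endpoints. The SAP's own definitions allow AUClast to be cut off earlier at low doses. The direction of bias is then upward, and the plan has no safeguard. With half-lives of 1 and 4 h and CV 40%, upward false rejection against a nominal 5% is about 8-18% with the LLOQ at 1-5% of the 0.5 mg Cmax, 13-28% at 10%, 18-55% at 20% and 60-89% at 50%. At CV 40%, false rejection becomes more likely than not when Cmax at 0.5 mg is within about 5 times the LLOQ (half-life 4-12 h) or about 2 times (half-life 1 h).

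These rates rest on an assumed LLOQ, half-life, CV and one-compartment model. AUCtau was not simulated. The overall proportionality conclusion need not be overturned, since Cmax is essentially free of the problem. Phase 2 dose selection is a reasonable concern because protocol 1.3 says this study informs it, though no section links that choice to the AUClast slope alone. The change should be made because it is cheap, but the plan does not fail without it.

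**What to change.** In SAP 8.1.4.1 and protocol 8.7:

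1. Base the proportionality conclusion on Cmax and a partial AUC over one common interval. The interval runs from 0 to the latest nominal time at which most active subjects at the lowest modelled dose are quantifiable. Subjects whose tlast is earlier are integrated to their own tlast and not dropped.
2. Use AUCinf (single dose) only for dose levels that meet a pre-stated limit on %AUCextrap and have enough subjects with an estimable Kel.
3. Report the AUClast slope descriptively, without the slope-1 test.
4. Apply the same rules to the dose-normalised ANOVA.

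The cost is a few lines of text and one extra derived parameter from samples already planned. There are three downsides. The common interval covers less of the curve. A low dose may drop out of the AUCinf model: with a 20% extrapolation limit applied to cohort medians, 0.5 mg stayed in only 0-7% of simulated trials at half-life 3 h and LLOQ 20-30% of Cmax. A small upward bias also remains (about 15% rejection) if the lowest dose is barely quantifiable.

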### **3. STUDY DESIGN**

#### **3.1. Study Design Description**

This protocol describes a single- and multiple-ascending dose FIH Phase 1 study to evaluate the safety, tolerability, PK, and PD of TLC-2716 in healthy adult subjects.

The study will be conducted at a single Phase 1 center in New Zealand. A total of up to 150 subjects will be enrolled, including 100 subjects in Parts A and B, and up to 50 subjects in adaptive cohorts in Part C. Within each cohort, 10 subjects will be randomized, including 8 subjects randomized to TLC-2716 and 2 subjects to PTM. In single-dose cohorts in Parts A and in any Part C cohort evaluating a higher total daily dose than previously evaluated, safety and tolerability data collected through Day 2 from two sentinel subjects, one randomized to TLC-2716 and one to PTM, will be evaluated prior to dosing of the remaining subjects in each cohort.

An approximately even distribution of healthy male and non-pregnant, non-lactating female subjects 18 to 55 years of age, inclusive, will be enrolled in the study. Subjects may not participate in more than one cohort of the study. Following the completion of Screening and admission assessments, eligible subjects will be enrolled on Day -1.

The duration of dosing will be 1 day for the SAD cohorts in Part A and C, and 15 days for the MAD cohorts in Parts B and C, including PTM dosing on Day -1 for all subjects in MAD cohorts.

The overall study duration, post-screening, will be up to 18 days for Part A, and up to 32 days for Parts B and C.

This study will proceed in 3 parts, with progression within and between parts governed by reviews of safety and any available and relevant PK and/or PD data, and the application of stopping rules. The sponsor, in consultation with the investigator, may choose not to initiate any or all adaptive cohorts in Part C if deemed unnecessary based on observations in Parts A and B. The overall study design and the design of each part are described below, and the study schemas are presented in [Figure 1](#) for SAD cohorts in Parts A and C, and [Figure 2](#) for MAD cohorts in Parts B and C.

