##### **3.1.1. Part A: Single-Ascending Dose [SAD] (Cohorts 1-5)**

Part A will evaluate the safety, tolerability, PK, and PD of single-ascending doses of oral TLC-2716 or placebo under fed conditions. Part A will proceed in up to 5 dose-escalation cohorts and will be governed by a review of safety, tolerability, and any available and relevant PK and/or PD data, and study-specific stopping criteria. Planned study treatments within each cohort are provided in [Table 2](#).

- Within each cohort, 10 unique subjects will be randomized 4:1 to receive either blinded TLC-2716 (N = 8) or PTM (N = 2). All study drugs in Part A will be administered in the morning following a standard meal.
- At the initiation of each cohort in Part A, prior to randomization of the entire cohort, two sentinel subjects will be randomized, one to TLC-2716 at the dose to be evaluated in the planned cohort, and one to corresponding PTM. Enrollment and randomization of the remaining eight subjects in each cohort will be determined upon evaluation of all safety and tolerability data through Day 2 for these two sentinel subjects.
- For cohorts 2-5, initiation of single-dose administration will be permitted after evaluation of cumulative blinded safety data, and any relevant and available PK and/or PD data up to and including Day 4, following single-dose administration of the previous cohort.

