### 3.1.2. Part B: Multiple-Ascending Dose [MAD] (Cohorts 6-10)

Part B will evaluate the safety, tolerability, PK, and PD of multiple-ascending doses of oral TLC-2716 or placebo under fed conditions. Part B will proceed in up to 5 dose-escalation cohorts and will be governed by a review of safety, tolerability, and any available and relevant PK and/or PD data, and study-specific stopping criteria. Planned study treatments within each cohort are provided in [Table 3](#).

- Randomized, blinded (sponsor-unblinded), placebo-controlled, multiple-ascending doses of TLC-2716 in healthy subjects. An attempt will be made to enroll at least 3 subjects in each cohort with Screening TG ≥ 150 mg/dL and/or low-density lipoprotein cholesterol (LDL-C) ≥ 130 mg/dL.
- Within each cohort, 10 unique subjects will be randomized 4:1 to receive either blinded TLC-2716 (N = 8) or PTM (N = 2) QD for 14 days.
- Part B (Cohort 6) may be initiated after the evaluation of cumulative safety, tolerability, and any relevant and available PK and/or PD data from all subjects enrolled in Cohort 3 in Part A (up to and including Day 4).

- For Cohorts 7-10, dosing may be initiated after evaluation of cumulative safety, tolerability, and any relevant and available PK and/or PD data from all subjects enrolled in the previous cohort in Part B through Day 14.
- All study drugs in Part B will be administered in the morning following a standard meal.

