##### **8.1.5. Evaluation of Food Effect**

For statistical evaluation of food-effect, PK parameters ( $AUC_{\text{last}}$ ,  $AUC_{\text{inf}}$ , and  $C_{\max}$ ) of TLC-2716 under fasted conditions versus fed conditions for selected cohort(s) will be compared by ANOVA using a linear mixed effect model with fed/fasted status as a fixed effect and participant as a random effect, unless otherwise stated. The ratio of geometric means and associated 90% CI will also be calculated for  $AUC_{\text{last}}$ ,  $AUC_{\text{inf}}$  and  $C_{\max}$  between the fed and fasted conditions.

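### The SAP limits the dose-proportionality power model to fasted dosing, but every prespecified cohort is dosed fed, so as written it gives no slope for Part A or Part B

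*Combined protocol and SAP*

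**What the plan says.** SAP 8.1.4.1 opens with a broad scope: dose proportionality, "as applicable for Part A, Part B, and Part C (as applicable) over the dose range tested will be investigated". The next sentence fits the power model, ln(Y) = β0 + β1 ln(X), with the parameter as Y "and X (dose) under fasting conditions".

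Protocol 8.7 describes the same analysis without a meal condition: "A power model will be fitted using all doses across cohorts to evaluate the dose proportionality based on" the AUC parameters, Ctau and Cmax. It asks for a 90% CI on the slope and for single- and multiple-dose cohorts to be analysed separately.

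The dosing sections leave no doubt about meals in Cohorts 1-10. Protocol 3.1.1: "All study drugs in Part A will be administered in the morning following a standard meal". Protocol 3.1.2: "All study drugs in Part B will be administered in the morning following a standard meal". SAP 1.2.1 and 1.2.2 repeat this, and protocol 5.3.1 says the same. Fasted dosing is possible only in Part C, whose cohorts are optional and may be fed or fasted (protocol 3.1.3).

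For food effect, SAP 8.1.5 compares fasted with fed "using a linear mixed effect model with fed/fasted status as a fixed effect and participant as a random effect". Protocol 3.1 says: "Subjects may not participate in more than one cohort of the study". Protocol 3.1.3 holds meal conditions constant within a cohort.

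**The concern.** Characterising single- and multiple-dose PK is a primary objective, and the power model is the planned test of whether exposure rises in proportion to dose. The SAP attaches to it a meal condition that none of the prespecified cohorts meets. An analyst who follows the SAP has no Part A or Part B data to fit. One who ignores the clause departs from the SAP without a stated rule for which cohorts go in.

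Going back to the protocol wording does not fully settle it. Fitting all doses across cohorts would pool any fasted or modified-meal Part C cohort with the fed ones, and part of a dose effect could then be a meal effect.

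The food-effect section has a smaller mismatch of the same kind. A random participant effect suits repeated observations on a person under both meal conditions, and the protocol rules those out.

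**Working it through.** **The plan's own figure.** No power, SD or CV is stated. The sample size reproduces: 10 cohorts × 10 = 100 and 15 × 10 = 150, with 8 active and 2 placebo per cohort.

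**Who qualifies under the literal clause.** Parts A and B each have 5 cohorts × 8 active = 40, so 80 active subjects. Fasted among them: 0. Part C could supply between 0 and 5 × 8 = 40 fasted active subjects.

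**Slope precision.** For a straight line on ln(dose), the 90% half-width is t(0.95, n−2) × SD / √Sxx, where SD = √ln(1 + CV²) and Sxx is the sum of squares of ln(dose) about its mean. The CVs are assumptions: 30%, 50% and 70% give SD = 0.294, 0.472 and 0.631.

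- *Five fed doses* (0.5, 2, 6, 12, 20 mg; 8 each; n = 40): Sxx = 69.94, √Sxx = 8.36, t(38) = 1.686.
- *One fasted dose level* (n = 8): Sxx = 0, so no slope exists.
- *Two fasted dose levels in cohorts of the same type*, 20 and 50 mg for illustration (n = 16): Sxx = 16 × (ln 2.5 / 2)² = 3.36, √Sxx = 1.83, t(14) = 1.761.
- *Two closer levels*, 12 and 20 mg for illustration (n = 16): Sxx = 1.04.

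| Data | CV 30% | CV 50% | CV 70% |
|---|---|---|---|
| Five fed doses | 0.059 | 0.095 | 0.127 |
| Fasted 20 and 50 mg | 0.282 | 0.454 | 0.607 |
| Fasted 12 and 20 mg | 0.506 | 0.814 | 1.089 |

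**Food effect.** With one value per subject, the covariance matrix is (σ²participant + σ²residual) × I, so only the sum of the two variances enters the likelihood. A check on one simulated 8 v 8 data set with total variance 0.22 gave the same REML log-likelihood (5.7159) and the same standard error, √(0.22 × 2/8) = 0.2345, whether 0%, 25%, 50% or 90% of the variance was assigned to participant. The fed/fasted estimate did not change either. The split between participant and residual cannot be estimated, but the contrast can. As a between-subject comparison, its 90% CI is the geometric mean ratio multiplied or divided by exp(t(0.95, 14) × SD × √(2/8)) = 1.30, 1.52 and 1.74 at CVs of 30%, 50% and 70%.

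**The case against.** The strongest reply is that the intended analysis is easy to recover. The SAP's scope sentence and protocol 8.7 both point to all parts, the alternative ANOVA in SAP 8.1.4.1 carries no fasting condition, and deleting three words removes the conflict. That is fair as to intent, and it is why the repair is cheap. It does not make the sentence right, and it leaves open how fasted Part C cohorts are handled.

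Three stronger readings are tempting, and the documents do not support them.

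- *The analysis has no data at all.* This is certain only for Parts A and B. Part C may be dosed fasted, and two fasted dose levels of the same type would give a slope, though a poor one.
- *The food-effect model assumes a crossover and cannot be fitted.* The SAP never mentions a crossover. The ratio and its CI remain estimable between cohorts, so the participant term is redundant rather than fatal. In a multiple-dose cohort, Day 1 and Day 14 values could even make a participant variance estimable, but meal would still vary only between subjects. The comparison is also conditional on fasted cohorts being run.
- *The slope test will certify proportionality, so an equivalence margin is needed.* SAP 8.1.4.1 states a null hypothesis of slope 1, judged against the 90% CI, but not what will be declared from it. Failing to reject is not proof, but a fixed margin is a trade-off with no source in the documents. Take a 2-fold margin over the 40-fold range, 1 ± ln 2 / ln 40 = 0.81 to 1.19. At an assumed CV of 100% and a true slope of exactly 1, it is inconclusive about 82% of the time. At CV 30% and a true slope of 1.15, it concludes proportionality about 28% of the time, against 0.5% retained under the present rule.

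Nor does the whole PK objective rest on this model. The primary PK endpoints are the parameters themselves, summarised descriptively, and those summaries are unaffected.

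**Conclusion.** Wrong as written. The fasting clause in SAP 8.1.4.1 contradicts the fed dosing of all ten prespecified cohorts, the SAP's own scope sentence and protocol 8.7. Taken literally, 0 of 80 planned active subjects in Parts A and B enter the fit and neither part has a slope. Whatever remained would depend on optional fasted Part C cohorts. With two dose levels at 20 and 50 mg, the slope's 90% half-width would be roughly five times that from the five fed doses (0.282 / 0.059 = 4.8 at every assumed CV). The counts come from the documents. The half-widths rest on assumed CVs, full cohorts of 8 active subjects and illustrative Part C doses.

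The participant effect in SAP 8.1.5 is a secondary tidy-up: it does no numerical harm with one value per subject, but it misdescribes a comparison that is purely between subjects.

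**What to change.** 1. In SAP 8.1.4.1, replace the fasting clause with a definition of the main fit: fed, once-daily cohorts, meaning Parts A and B plus any once-daily Part C cohort given the same standard meal. Fit single-dose and multiple-dose data separately, as protocol 8.7 requires. Keep fasted and modified-meal cohorts out of the main fit and report them separately, so that dose is not confounded with meal.
2. Report the slope with its 90% CI and the exposure ratio it implies, rather than a pass/fail verdict. Over 0.5 to 20 mg the departure from proportionality is 40^(β1 − 1); a slope of 1.15, for example, means 40^0.15 = 1.74-fold. No equivalence margin is needed.
3. In SAP 8.1.5, specify an ANOVA on ln-transformed parameters with fed/fasted status as the only effect, for cohorts matched on dose and regimen. Drop the participant random effect and label the result a between-subject comparison.

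The cost is SAP wording only, with no change to dosing, sampling or sample size. The one loss is that fasted or modified-meal Part C cohorts do not add to the main slope. If the SAP is already final, its Section 1 requires the change to be documented in the clinical study report.
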